**5.2.- Scope of the study**

Patients operated on in the Cardiac Surgery Department of Hospital Universitario Puerta del Mar in Cádiz.

**5.3.- Study subjects**

Adult patients of both sexes who undergo cardiac surgery and need intraoperative support from the CPB pump at Hospital Universitario Puerta del Mar in Cádiz between February 2017 and August of the same year.

**5.4.- Description of methods:**

The proposed methods to be used in this study are based on analyses of the following instruments and variables:

- Clinical and analytical instruments.
- Record sheet of variables from the patient's medical record.
- Record sheet of intraoperative variables.
- Graph from the perfusionist and electronic data collection systems.
- Record sheet of postoperative variables.
  - Graph and records from the ICU.
  - Graph and records from the ward.
  - Lactate testing instruments.

The variables to be studied have been selected according to the existing literature regarding the factors associated with the results of the therapy used.

- Dependent variables:
  - Levels of serum lactate in mmol/L (continuous quantitative variable): at the beginning of CPB, after 10 minutes of CPB, every 20 minutes during the procedure and 20 minutes after the end of CPB.
  - Effluent lactate levels in mmol/L (continuous quantitative variable): at the end of the procedure.
  - Intra- or perioperative mortality, yes/no (dichotomous variable).
  - Complications: intubation, seizures, pleural effusion requiring drainage, yes/no (dichotomous variable).
  - Evaluation of the outcome of the intervention by the perfusionist nurse. During CPB. NOC nursing taxonomy in the preoperative period, at the end of each procedure and in the postoperative period. These outcomes consist of indicators that measure the patient's health on a Likert scale (1-5).
- Adjustment or stratification variables:
  - Predicted mortality scale (EuroSCORE[[1]](#footnote-2)).
  - Serum potassium and lactate values, immediately after surgery and with each routine blood analysis in the ICU.
- Preoperative variables:
  - Demographic variables:
    - Age: years (quantitative variable).
    - Sex: male/female (dichotomous variable).
- Biometric variables:
  - Height: centimeters (continuous variable).
  - Weight: kilograms (continuous variable).
    - The above variables will be used to calculate the body mass index (BMI): weight/height2 = kilograms/m2 (continuous variable).
- Biochemical variables:
  - Glucose: mg/dL (continuous variable).
  - Serum lactate: mmol/L (continuous variable).
  - Diagnosis upon admission: according to ICD-9 international classification.
    - Comorbidities: presence/absence in the patient's medical record (dichotomous variables):
      - Arterial hypertension.
      - Hyperlipidemia.
      - Peripheral artery disease.
      - Chronic obstructive pulmonary disease.
      - Impaired renal function.
      - Impaired hepatic function.
      - Type 2 diabetes mellitus.
      - Cerebrovascular disease.
      - Pulmonary hypertension.
    - Myocardial function prior to surgery:
      - Left ventricular dysfunction (whether or not due to previous myocardial infarctions), measured according to the ejection fraction (EF) described in the most recent echocardiography/ventriculography and categorized into:
        - Normal EF > 55%.
        - Mildly impaired function 45-55%.
        - Moderately impaired function 30-45%.
        - Severely impaired function <30%.
        - Functional assessment of heart failure (ordinal variable: NYHA (New York Heart Association) functional class I to IV.
    - Existence of previous liver disease: yes/no (dichotomous variable).
    - Drug allergies: yes/no (dichotomous variable).
    - Smoking history: yes/no (dichotomous variable). If “yes”: current number of cigarettes/day (quantitative variable).
    - Postoperative renal failure: yes/no (dichotomous variable).
    - Classification of acute kidney injury according to the AKIN classification: stages 1/2/3 according to serum creatinine and diuresis (categorical variable).
    - Risk stratification: the EuroSCORE logistical I [21] (Annex I) will be used for preoperative surgical risk assessment: categorical variable.
    - Medical treatment and dosage: yes/no (dichotomous variable) and milligrams/day, of:
      - Antihypertensives.
      - Diuretics.
      - Beta-blockers.
      - Calcium channel blockers.
      - Digitalis.
      - Antiplatelet therapy and withdrawal time prior to surgery.
    - Complexity (categorical variable):
      - Non-coronary surgery.
      - Coronary surgery, single procedure.
      - Coronary surgery, two procedures.
      - Coronary surgery, three or more procedures.
      - Surgery on thoracic aorta.
- Intraoperative variables:
  - Anaesthetic variables:
    - Induction and maintenance: active substances (categorical variable).
    - Volume used in anaesthetic induction prior to CPB: ml (continuous variable).
    - Monitoring: Use of pulmonary artery catheter, yes/no (dichotomous variable).
    - Use of vasoactive and inotropic agents: drugs (categorical variable) immediately after coming off the pump and upon arrival in the ICU.
    - CPB or extracorporeal perfusion variables:
      - Blood products:
        - Haemoglobin in mg/dl and baseline haematocrit measured at the start of CPB (continuous quantitative viable). Use of blood products in priming and/or during the procedure, yes/no (dichotomous variable).
      - Additives:
        - Use of corticotherapy, yes/no (dichotomous variable).
        - Use of insulin, yes/no (dichotomous variable).
      - Times:
        - Surgery time, in minutes (continuous variable).
        - Aortic cross-clamping time in minutes (continuous variable).
        - Support time, in minutes (continuous variable).
        - Haemofiltration time, in minutes (continuous variable).
        - Time from unclamping to patient decannulation, in minutes (continuous variable).
      - Haemofiltration:
        - Duration, in minutes (continuous variable).
        - Total volume (VTot) extracted in the effluent and Replacement volume (VolR) with plasma solution during CPB, in thousands (continuous variable).
        - Water balance during CPB (VTot-VolR), in millimeters (continuous variable).
      - Metabolic and homeostatic control:
        - Blood gas, acidosis yes/no (dichotomous variable).
        - Glucose, in mg/dl (continuous variable).
        - Temperature, in degrees centigrade (continuous variable).
        - Anion gap in mEq/L (in order to diagnose potential lactic acidosis in cases of poorly-defined metabolic acidosis with levels above 12 mEq/L) [22] (continuous variable).
  - Surgical variables:
    - Surgical procedure performed.
      - Valve surgery, yes/no (dichotomous variable).
      - Coronary surgery, yes/no (dichotomous variable).
      - Combined surgery, yes/no (dichotomous variable).
  - Postoperative variables in ICU.
    - Clinical and scale variables:
      - Intubation time, in hours. (continuous variable).
      - Time of stay in ICU, in hours. (continuous variable).
      - Number of hours on inotropic and/or vasoactive support. (continuous variable).
      - Blood loss.
        - Transfusion of blood products, yes/no (dichotomous variable).
        - Postoperative hospital stay, in days (quantitative variable).
        - Hospital mortality, death yes/no (dichotomous variable).

Hematocrit in percentage (continuous variable).

SOFA score [23] (Annex II) (categorical variable).

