Intraoperative HL in heart surgery is observed in between 10% and 21% of patients once CPB begins, persisting until the patient reaches the ICU, and it is related to a higher rate of postoperative complications and mortality.

By correcting the risk factors that cause HL during CPB it is possible to control this metabolic disorder and improve patients' prognostic.

In the Perfusion Unit of the Cardiovascular Surgery Unit of Hospital Universitario Puerta del Mar in Cádiz, surgery with CPB that does not require circulatory arrest is performed under normothermic conditions using an alpha-stat acid-base management strategy, as there is no need to correct the pH values based on the temperature. Similarly, the central venous saturation values (SvO2) as an indication of the ratio between oxygen consumption and oxygen supply in relation to the patient's body surface area (DO2i), oxygen extraction (ERO2) and difference between carbon dioxide tension in arterial and venous blood (△pCO2) will be recorded every 20 minutes.

The △pCO2 is a very important value that helps the perfusionist detect capillary hypoperfusion in surgical patients during CPB, as a difference in arterial and venous pCO2 above 8 mmHg, even with optimum SvO2 values of >70%, is related to an increase in intraoperative lactate and a decrease in splanchnic function [10].

But there are intraoperative situations in which HL cannot be controlled during CPB, as is the case of patients with hepatic failure, renal failure, intraoperative blood transfusions and pre-surgical HL. In these patients, the evolution of HL is made worse by longer duration of CPB and hypotension during the procedure [11].

Hemofiltration is performed at two clearly distinct points during heart surgery. During CPB it is called conventional ultrafiltration (CUF) and it depends directly on the content of the venous reservoir in the CPB circuit. Modified ultrafiltration (MUF) is independent of this circuit and is performed once the CPB procedure is finished. Both use a highly permeable polysulfone hollow fibre filter housed in a polyvinyl chloride (PVC) cylinder. A pressure gradient and concentration are used to extract liquids, electrolytes and non-protein-bound solutes with a molecular weight below 50,000 Daltons.

Traditionally, CUF is performed in patients with acute kidney injury (AKI), fluid overload (CPB pump priming fluid, cardioplegic solution) and intraoperative hyperkalemia.

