**4.2.- Hypothesis:**

- Continuous ultrafiltration with volume replacement using a polysulfone membrane during CPB in patients undergoing cardiac surgery decreases intraoperative lactatemia.
- Patients undergoing cardiac surgery and continuous ultrafiltration with volume replacement using a polysulfone membrane have a lower postoperative morbidity and mortality rate than patients undergoing cardiac surgery without hemofiltration.
- Patients undergoing cardiac surgery and continuous ultrafiltration with volume replacement using a polysulfone membrane have a better health status after surgery than patients undergoing cardiac surgery without hemofiltration. (Assessed by NNN taxonomies: NANDA, NOC, NIC).

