**5.7.- Statistical analysis [24]:**

- Descriptive analysis of variables: measures of central tendency and dispersion will be shown in the case of quantitative variables, while frequencies and proportions will be shown in the case of categorical variables.
- The normality of the variables will be checked using graphs and the Kolmogorov-Smirnov test.
- Homogeneity and comparability between the groups of the two arms of the study in the main confounding factors considered will be verified at the beginning of the study by means of a comparison of proportions (chi-squared test or Fisher's exact test, if necessary) and a comparison of means (Student's t-test and the Mann-Whitney U test in case of non-parametric distributions).
- The intrasubject change over time will be analyzed by comparing paired means using a t-test or Wilcoxon signed rank test (non-parametric variables), quantifying the change in each measure in relation to the baseline reference measure (first sample).
- The bivariate analysis between the CG and PG will be performed using the chi-squared test or Fisher's exact test, if necessary, and using a comparison of means (Student's t-test and Mann-Whitney U test in case of non-parametric distributions).
- In the event of non-homogeneity in any variable between the groups studied, a multivariate analysis will be performed using linear regression.

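### Postoperative lactate and potassium are named as adjustment variables, so an adjusted or stratified analysis could attenuate the effect on lactate

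*Protocol*

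**What the plan says.** Protocol section 5.4 has a heading "Adjustment or stratification variables" with two entries. One is EuroSCORE, which is fixed before surgery. The other is "Serum potassium and lactate values, immediately after surgery and with each routine blood analysis in the ICU".

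The first dependent variable in the same section is serum lactate, sampled "at the beginning of CPB, after 10 minutes of CPB, every 20 minutes during the procedure and 20 minutes after the end of CPB". The first hypothesis in section 4.2 is that continuous ultrafiltration "using a polysulfone membrane during CPB in patients undergoing cardiac surgery decreases intraoperative lactatemia". The second is that filtered patients "have a lower postoperative morbidity and mortality rate than patients undergoing cardiac surgery without hemofiltration".

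Section 5.4 also records a serum lactate among the biochemical variables. From its position, ahead of the comorbidities and the intraoperative data, this is a preoperative value. It is not under the adjustment heading.

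Further down the preoperative list stands "Postoperative renal failure: yes/no (dichotomous variable"), followed by AKIN stage, for which no time of assessment is given.

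The last item of section 5.7 reads: "In the event of non-homogeneity in any variable between the groups studied, a multivariate analysis will be performed using linear regression". An earlier item in that section describes a check of comparability on the main confounders, made at the start of the study.

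**The concern.** An adjustment variable should not be open to influence by the treatment. Both analytes in the second entry are measured after randomisation and after the whole intervention.

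- **Lactate.** The sample taken straight after surgery measures the same analyte as the main outcome, whose own last sample is 20 minutes after bypass ends. Section 3 says that intraoperative hyperlactatemia is seen "persisting until the patient reaches the ICU, and it is related to a higher rate of postoperative complications and mortality". On the protocol's own account, then, an intraoperative effect can carry over into the covariate.
- **Potassium.** Section 3 gives intraoperative hyperkalemia as a traditional reason for conventional ultrafiltration and lists potassium chloride in the replacement solution. Treatment can therefore change potassium.

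Comparing arms at equal postoperative lactate asks whether filtration lowers intraoperative lactate among patients whose lactate ended up the same, which is not the trial's question. For the second hypothesis, holding ICU lactate fixed would block a route by which the treatment is supposed to act. Stratifying on these values has the same fault as regressing on them.

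The trigger adds to the difficulty. If postoperative values count as variables whose imbalance calls for regression, the adjustment is most likely to be made when the treatment has worked.

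**Working it through.** The protocol gives no figure on this point to reproduce. It states no effect size, SD, alpha or power; the sample size, about 40 in section 5.6, comes from a recruitment period. What follows is an illustration under stated assumptions.

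**Model.** Let T be the arm, Y intraoperative lactate and M postoperative lactate, both with within-arm SD 1:

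- Y = d·T + e
- M = m·d·T + u, with corr(e, u) = rho

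Here d is the true effect, m the share of it still present after surgery, and rho the within-arm correlation. With equal SDs, E(e | u) = rho·u. Substituting u = M − m·d·T gives

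E(Y | T, M) = d(1 − rho·m)·T + rho·M.

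The adjusted coefficient on arm is therefore d(1 − rho·m). Nothing is lost only if rho = 0 or m = 0.

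**Precision.** Assume 20 patients per arm (half of about 40), d = 1 SD and a two-sided 5% test. Under the normal approximation:

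- Unadjusted SE = √(2/20) = 0.316, and power = Φ(1/0.316 − 1.96) = 0.885.
- Adjusted SE = √[(1 − rho²)·(2/20)·(1 + m²d²/4)]. At m = 1, rho = 0.7 this is √(0.51 × 0.1 × 1.25) = 0.252, and power = Φ(0.30/0.252 − 1.96) = 0.22.

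| m | rho | Adjusted effect (true = 1.00) | Share lost | Power (unadjusted 0.885) |
|---|---|---|---|---|
| 0.5 | 0.3 | 0.85 | 15% | 0.78 |
| 0.5 | 0.5 | 0.75 | 25% | 0.76 |
| 0.5 | 0.9 | 0.55 | 45% | 0.97 |
| 0.75 | 0.7 | 0.475 | 52.5% | 0.50 |
| 1 | 0.7 | 0.30 | 70% | 0.22 |
| 1 | 0.9 | 0.10 | 90% | 0.095 |

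Simulation of 5,000 trials per setting agrees: mean adjusted effects of 0.30 (m = 1, rho = 0.7), 0.10 (m = 1, rho = 0.9), 0.47 (m = 0.75, rho = 0.7) and 0.76 (m = 0.5, rho = 0.5), against unadjusted means of 0.99 to 1.00.

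The third row shows that power need not fall. A strongly correlated covariate also removes residual variance, so a test can stay sensitive while the estimate is about half its true size. The dependable consequence is bias in the estimate.

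**Trigger.** Suppose postoperative lactate is itself tested for imbalance with a t-test at 5%. In the same simulations a true 1 SD effect brings the adjustment into play in about 34% of trials at m = 0.5, 63% at m = 0.75 and 86 to 87% at m = 1. This applies only if the regression rule covers postoperative variables.

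**The case against.** The strongest reply concerns how the regression starts. Section 5.7 checks homogeneity on the main confounders at the start of the study, and the regression rule reuses that idea. Read together, the rule follows up a baseline check, and ICU lactate could not trigger it. That reading is reasonable, but it is not written down. The rule says any variable, stands directly after the between-group comparison rather than after the baseline check, and section 5.4 names the postoperative values as adjusters. No section limits adjustment to pre-randomisation data.

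The comparison of arms by t-test or Mann-Whitney is unadjusted and unaffected, and the regression is conditional. This stands in full. The protocol also does not say which model would use the listed values. A statistical analysis plan could settle that, but the list it would inherit is already wrong.

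A reader might infer that the adjusted analysis would cancel the treatment effect. The documents do not support this. Near-complete loss needs both full persistence and very high correlation, and the protocol gives a figure for neither. Routine ICU samples also continue well beyond the end of surgery, so the carry-over into them may be weaker than for the sample taken straight after it.

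Three further limits hold. The effect on potassium has no stated size or direction: filtrate is replaced with a solution that contains potassium, and adjusting for potassium biases the result only so far as it also correlates with lactate within arm. Postoperative renal failure is misfiled under preoperative variables but is not named as an adjuster. AKIN stage has no time point, so it cannot be called postoperative on the text.

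**Conclusion.** The point holds as a fault in the variable list and in a loosely worded rule. Section 5.4 names a later reading of the main outcome, and an electrolyte that treatment can change, as adjustment or stratification variables. It leaves the preoperative lactate off that list. Section 5.7 does not restrict the regression to baseline data.

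An analysis that followed the list could bias the estimated effect towards zero, by 15% to 90% over m from 0.5 to 1 and rho from 0.3 to 0.9. That range assumes equal SDs, a linear model and adjustment for a single postoperative lactate value; m, rho and the 1 SD effect are assumptions. Only lactate is quantified. For potassium the concern is one of principle. The unadjusted result stands whatever is decided here, so what is at risk is a conditional adjusted or stratified estimate that might contradict it.

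**What to change.** In section 5.4:

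- Move postoperative serum lactate, potassium and postoperative renal failure to the outcome variables.
- State when AKIN stage is assessed, and treat it as an outcome if that is after surgery.
- Keep under the adjustment heading only variables fixed before randomisation, for example EuroSCORE and preoperative serum lactate. Other baseline variables would be equally valid if named in advance.

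In section 5.7, replace the reference to any variable with a statement that adjustment uses only pre-randomisation variables. This edit is needed as well: moving items between lists in 5.4 does not close the route through the regression rule, because an item moved to the outcomes is still a variable.

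The cost is text edits in two sections. Preoperative lactate and EuroSCORE are already collected, and no new data or patients are needed.

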MUF seeks to achieve more effective hemofiltration by hemoconcentrating the patient and reducing inflammatory mediators [12].

The surgical team at Puerta del Mar University Hospital who are taking part in the research usually use a polysulfone membrane throughout the procedure and perform high-flow continuous ultrafiltration (UF), replacing the filtered volume with Prismasol 2® pharmaceutical solution, which contains the following active substances: calcium chloride, dihydrate; magnesium chloride, hexahydrate; glucose monohydrate, lactic acid solution 90%; sodium chloride; potassium chloride and sodium hydrogen carbonate. This solution is also used for priming the CPB circuit, and it must be taken into account in the research that Prismasol 2® solution contains 3 mEq/L of lactate.

Prismasol 2® solution is used as a solution for hemofiltration in the treatment of renal insufficiency and no contraindications with CPB have been reported, since serum potassium and calcium levels are monitored every 20 minutes. The administration of sodium bicarbonate is also eliminated from priming.

Likewise, CUF during CPB is safe thanks to continuous patient monitoring throughout the procedure.

The flow rates recommended by the manufacturer for the replacement solution in hemofiltration and hemodiafiltration are as follows: Adults and adolescents: 500 - 3000 ml/hour.

The use of hemofiltration in adults during CPB procedures has evolved over the years, with studies showing the advantages of CUF or MUF in CPB procedures, such as increased hematocrit with the consequent reduction in blood transfusions, reduction of inflammatory response, improvement of hemodynamic parameters and better neurological outcomes in patients, as well as a shorter postoperative intubation time in the intensive care unit [13].

There is a disparity in the scientific literature regarding HL during and after CPB, and while Soliman R et al. [14] consider that continuous hemofiltration increases postoperative lactate levels and inotropic drug use, Kiziltepe et al. [15] describe it as a safe procedure in adult patients undergoing cardiac surgery.

Perhaps the results of the Soliman group were conditioned by the use of moderately hypothermic CPB and the use of Ringer's lactate solution at a concentration of 27.8 mEq/L for priming the CPB circuit.

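### Section 5.4 lists lactate and potassium measured after surgery and in the ICU as adjustment or stratification variables, although hemofiltration can change both

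*Protocol*

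**What the plan says.** Section 5.4 sorts the trial's variables by role. Under adjustment or stratification variables it has two entries: EuroSCORE, and "Serum potassium and lactate values, immediately after surgery and with each routine blood analysis in the ICU". Serum lactate from the start of bypass until 20 minutes after it ends is a dependent variable in the same section. Preoperative serum lactate appears separately among the biochemical variables.

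Section 5.7 has two bullets that bear on adjustment. One checks comparability of the arms: homogeneity "in the main confounding factors considered will be verified at the beginning of the study". The last bullet sets the trigger for an adjusted analysis: "In the event of non-homogeneity in any variable between the groups studied, a multivariate analysis will be performed using linear regression". Neither names a covariate.

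Other sections indicate that the filter can move both analytes:

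- **Lactate.** The first hypothesis in 4.2 is that continuous ultrafiltration "during CPB in patients undergoing cardiac surgery decreases intraoperative lactatemia". Section 3 describes intraoperative hyperlactatemia as "persisting until the patient reaches the ICU".
- **Potassium.** Among the traditional reasons for conventional ultrafiltration, section 3 gives "fluid overload (CPB pump priming fluid, cardioplegic solution) and intraoperative hyperkalemia". The replacement fluid described there contains "potassium chloride and sodium hydrogen carbonate".

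**The concern.** A covariate used to adjust a randomised comparison should be one that treatment cannot have altered. Hemofiltration runs during bypass, so every value in the second 5.4 entry comes after it. Lactate taken immediately after surgery is also close to a later reading of the outcome, since the outcome series runs to 20 minutes after bypass. Adjusting for it, or stratifying the analysis by it, conditions on a consequence of treatment.

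Two errors can follow, in opposite directions. If the filter lowers lactate on bypass and the reduction carries over, adjustment removes part of the real effect. If lactate is higher after surgery in the filter arm without any on-bypass effect, adjustment creates an apparent benefit.

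The 5.7 trigger adds to the problem if taken literally. A filter whose effect lasts into the postoperative period itself produces the group difference that calls for the adjustment.

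**Working it through.** There is no figure in the protocol to reproduce on this point. Section 5.6 gives about 40 patients as a recruitment estimate, with no effect size, SD, alpha or power. What follows is an illustration.

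**Inputs**

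- From the protocol: about 40 patients (5.6) and two arms (5.1).
- Assumed: 20 per arm; normal data with SD 1 for both on-bypass lactate Y and postoperative lactate M; within-arm correlation ρ of 0.3, 0.5 or 0.7; two-sided 5% tests; a true on-bypass effect of -0.8 SD or none.

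**Step 1: what adjustment does to the estimate.** With unit SDs, regressing Y on arm and M gives an arm coefficient with expectation

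adjusted effect = d_Y - ρ × d_M,

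where d_Y and d_M are the true differences (filter minus control) in Y and M.

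- Full carry-over, d_Y = d_M = -0.8: the result is -0.8 × (1 - ρ), that is -0.56, -0.40 and -0.24 SD at ρ = 0.3, 0.5 and 0.7.
- Half carry-over, d_M = -0.4: -0.8 × (1 - 0.5ρ), that is -0.68, -0.60 and -0.52 SD.
- No on-bypass effect but a rebound, d_Y = 0 and d_M = +0.8: -0.8ρ, that is -0.24, -0.40 and -0.56 SD, an apparent benefit where none exists.

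Simulation with adjustment always applied (4,000 trials per case) agreed with the two carry-over lines. At ρ = 0.7 and full carry-over the mean estimate was -0.25 SD and power was 0.17, against about 0.70 unadjusted.

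**Step 2: adjustment only when triggered.** Section 5.7 adjusts on non-homogeneity, so the rule was simulated that way (100,000 trials per case). First, a t-test on M. If p < 0.05, least squares of Y on arm and M; otherwise a t-test on Y. The 0.05 threshold is an assumption, because 5.7 gives none. The trigger fires in 69% of trials when M differs by 0.8 SD, 24% at 0.4 SD and 5% at zero.

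| True d_Y | True d_M | Rejection rate at ρ = 0.3 / 0.5 / 0.7 | Mean estimate (SD) | Rejection rate, unadjusted |
|---|---|---|---|---|
| -0.8 | -0.8 | 0.43 / 0.32 / 0.22 | -0.60 / -0.47 / -0.34 | 0.69 |
| -0.8 | -0.4 | 0.62 / 0.60 / 0.59 | -0.74 / -0.70 / -0.67 | 0.69 |
| -0.8 | 0 | 0.69 / 0.70 / 0.71 | not tabulated | 0.69 |
| 0 | +0.8 | 0.09 / 0.19 / 0.42 | not tabulated | 0.05 |
| 0 | +0.4 | 0.05 / 0.06 / 0.07 | not tabulated | 0.05 |

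In the first three rows the rejection rate is power; in the last two it is the false rejection rate. Potassium was not simulated. The same formula applies, with potassium's own correlation with the outcome and its own treatment difference.

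**The case against.** The strongest reply is that 5.4 is a loosely arranged data catalogue and 5.7 intends baseline adjustment only. Section 5.4 does misfile other items: postoperative renal failure sits among the preoperative variables, and the ICU variables are nested under the intraoperative ones. Section 5.7 never refers back to the adjustment list. Its last bullet takes up the homogeneity language of the bullet that checks confounders at the start of the study. A literal reading of any variable would also let a difference in the outcome itself trigger regression, which cannot be intended. Nowhere does the protocol say that on-bypass lactate will be regressed on ICU lactate.

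This stands as far as it goes. The baseline-only reading is available, and under it the bias does not arise. But ICU values cannot be checked at the start of a study, so on that reading the 5.4 entry has no valid use. On the literal reading it permits a biased analysis. Nor is the protocol strict about post-randomisation variables elsewhere: 5.8 contemplates stratifying on procedure duration. A separate analysis plan might name the covariates, but the role assigned in 5.4 is this document's own statement.

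Two limits on the size also stand. The remark in section 3 on persistence concerns patients who develop hyperlactatemia and does not show that a between-arm difference persists. The rebound case has little support here: section 3 suggests that the lactate rise in a cited study was perhaps "conditioned by the use of moderately hypothermic CPB" and by a lactate-rich prime (27.8 mEq/L), whereas this trial is normothermic and its solution contains 3 mEq/L.

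**Conclusion.** The concern holds. Postoperative and ICU lactate and potassium are given the wrong role in 5.4, and 5.7 does not clearly stop them from being used in it. Whether harm follows depends on how 5.7 is applied, and its size depends on how much of the treatment difference is present after surgery.

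On the assumed inputs, material harm needs a large carry-over or rebound. Full carry-over cuts power from 69% to between 43% and 22%. A +0.8 SD rebound raises false rejection from 5% to between 9% and 42%. Half carry-over costs 7 to 10 percentage points of power, and a +0.4 SD rebound gives 5% to 7% false rejection. The direction of the bias follows from the formula; its size rests on assumptions, since the protocol supplies only the approximate number of patients. The wording should be corrected, because a trial of about 40 patients has little power to spare and the change needs no new data.

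**What to change.** - **Section 5.4:** remove postoperative and ICU lactate and potassium from the adjustment or stratification variables. List them as postoperative (secondary) outcomes, compared between arms under 5.7. Keep EuroSCORE.
- **Lactate adjustment, if wanted:** use the preoperative serum lactate already listed in 5.4.
- **Section 5.7:** limit the regression for non-homogeneity to variables measured before randomisation. The protocol does not say when randomisation takes place. If the team wants to use a first sample taken between randomisation and the start of hemofiltration, it should say so explicitly and set the limit at the start of hemofiltration.

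The cost is wording in two sections; the values are already collected. Because ICU samples follow routine care, the later values will fall at uneven times and are best reported descriptively.
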